### Outcome measures

#### Feasibility outcomes

This will include recruitment and dropout proportions, protocol adherence, as well as patient and provider satisfaction at 3, 6 and 9 months.

#### Primary outcome measures

This will include percent success in reaching BP control (Table 2) and changes in clinic BP measurements.

**Table 2 Tab2:** Definition of outcome measures

Variable	Definition
Blood pressure control	Clinic blood pressure control will be defined at resting systolic blood pressure of <140 mmHg and or diastolic blood pressure of <90 mmHg
Medication adherence	Medication adherence will be categorized using Medication Possession Ratios into: Excellent 100 % Good 80–99 % and Poor <80 %.

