**Methods:**

This two-arm cluster randomized controlled feasibility pilot trial will involve 60 recent-stroke survivors. Using a computer-generated sequence, patients will be randomly allocated into four clusters of 15 patients each per physician: two clusters in the intervention arm and two in the control arm. Patients in the intervention arm will receive a simple pillbox, a Blue-toothed UA-767Plus BT BP device and smartphone for monitoring and reporting BP measurements and medication intake under nurse guidance for 3 months. Tailored motivational text messages will be delivered based upon levels of adherence to the medication intake. Both groups will be followed up for 6 months to compare BP control at months 3, 6 and 9 as primary outcome measure. Physicians assessing BP control will be blinded to arms into which patients are allocated. Secondary outcome measures will include medication adherence scores and Competence and Autonomous Self-regulation Scale scores. A qualitative study is planned after follow-up to explore the lived experiences of participants in the intervention arm.

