An iterative, theory-guided, design process was used by our group to develop an m-Health BP self-management control program for poor, rurally located Hispanic and African American hypertensive patients called the Smartphone Med Adherence Stops Hypertension: SMASH) [37, 38]. SMASH included multilevel components:Patient-level interventions included: (1) sequential automated reminder signals, (2) tailored Short Message Service (SMS)/voice mail motivational and reinforcement messages based upon adherence to daily medication adherence and BP monitoring (every 3 days); and provider-level interventions entailing: (a) emailed summary reports with stepped care guidelines attached every 2 weeks, (b) phone alerts to clinic nurse navigator when verified out-of-range BP measurements occur. Several 3- and 6-month pilot RCTs were conducted with Hispanics and African Americans with uncontrolled HTN. In each RCT, we observed high acceptability, self-efficacy for following a medical regimen, 95–100 % medication adherence, a mean of 95 % achieving guideline-designated BP control compared to an average of 18 % in standard care (SC) patients and large systolic blood pressure (SBP) reductions (mean: -32 mmHg) [39, 40]. SMASH is capable of adaptation to other poor, undereducated patients with HTN using an iterative patient/provider-centered design approach.

The Phone-based Intervention under Nurse Guidance after Stroke (PINGS) study is fashioned after the SMASH program. The objective of the PINGS study is to test whether a theoretical-model-based, m-Health technology-enabled, multilevel integrated approach is feasible in improving sustained BP control among 60 recent Ghanaian stroke patients within 1 month of their stroke, while building capacity in Ghana for longer-term testing of m-Health technology for chronic disease management in this resource-limited setting. A nurse navigator will be employed in the study design as a task-shifting strategy in the care of chronic diseases in SSA where there is a perennial paucity of neurologists and physicians [41].

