#### Recruitment

A list of eligible patients will be identified from hospital medical records by a research assistant (RA) with the identity of the patients’ doctors not included. The research coordinator (RC) will contact and schedule eligible patients for screening/recruitment and obtain informed consent voluntarily from patients who are interested in the study. Subjects whose SBP averages ≥140 mmHg from the last two readings of the 10-min protocol will have their height, weight and waist circumference measured. A set of questionnaires will be administered to assess study outcome measures (see Table 1). The study site admits an average of 43 stroke patients each month. Based upon the stroke with HTN incidence patterns in the KATH and SMASH pilot work [38–40, 47], we will recruit eight patients (four intervention group patients and four control group patients) per month for enrollment into the study.

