#### Primary outcome measures

For these measures, generalized linear mixed models (GLMM) will be used to compare the two groups with group as primary independent variable and percent success reaching BP control (or resting BP changes individually) as the primary dependent variable (Table 2) [64]. GLMM allow for missing data, measurement at different times and take into account the effect of clustering, i.e., correlation of repeated measurements within patients clustered within MD (Medical Doctor) provider. Group and time (baseline, 3, 6 and 9 months) will be fixed effects; demographics and secondary outcome measures (e.g., medication adherence via the MPR) will be adjustment covariates. We will assess changes over time via a time-by-intervention interaction term in multivariable models. We will estimate differences (for means or proportions) in ancillary moderator and mediator measures between the two groups via 95 % CIs as appropriate (e.g., self-efficacy, autonomous regulation, and so forth.). We will estimate differences (via 95 % CI) in proportions and average slopes between intervention versus control groups and evaluate linearity of trajectories as input for future RCT analysis strategy. We will estimate percent success reaching BP control for each subject over the trial (baseline, 3, 6 and 9 months), and the within-subject longitudinal trajectories (e.g., slopes), and then summarize as mean longitudinal trajectory within each treatment group (e.g., mean slopes with 95 % CI). Intracluster correlation coefficient (ICC) and variance estimates will be obtained of efficacy outcomes and covariance structure of the longitudinal scores for determination of sample size (and hence adequate power) for a future RCT. Multiple imputation methods will be used for missing end-of-study outcomes. Dropout rate, both selective and differential, is an important issue. If more than 10 % of data are missing, we will add an intermediate evaluation point in a future RCT to provide more data for use in endpoint imputation.

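### Systolic control at baseline is 0 % by eligibility, yet baseline is an outcome time in the BP-control model and the within-arm slopes, and starting SBP is not a named covariate

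*Protocol article*

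**What the plan says.** **Entry.** The Inclusion criteria require SBP of at least 140 mmHg at the last pre-stroke encounter, the post-stroke encounter and the screening visit. Under Recruitment, the baseline measurements and questionnaires go to "Subjects whose SBP averages ≥140 mmHg from the last two readings of the 10-min protocol".

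**Outcome.** Table 2 states: "Clinic blood pressure control will be defined at resting systolic blood pressure of <140 mmHg". With the diastolic limit, the criterion reads "resting systolic blood pressure of <140 mmHg and or diastolic blood pressure of <90 mmHg". The primary measures are "percent success in reaching BP control (Table 2) and changes in clinic BP measurements", and the Abstract plans to "compare BP control at months 3, 6 and 9 as primary outcome measure".

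**Analysis.** In the Statistical analyses section (Primary outcome measures), group and time are fixed effects, and baseline is one of the four levels of time. Change over time is assessed by a time-by-intervention term. The named adjustment covariates are demographics and secondary outcome measures. The section adds: "We will estimate percent success reaching BP control for each subject over the trial (baseline, 3, 6 and 9 months", followed by within-subject trajectories summarised as mean slopes with 95 % CI in each arm.

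**The concern.** The systolic limit that admits a patient is the one that the patient must later fall below. If control turns on SBP, every patient is uncontrolled at baseline because the eligibility rule makes it so. Three things follow.

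- **Model.** A binary outcome with no events at one time level, in both arms, has no finite log-odds there. A time-by-intervention contrast taken against that level is not estimable without a further constraint.
- **Within-arm slopes.** Any line that starts at a forced zero can only go up. Ordinary visit-to-visit variation then looks like improvement.
- **Adjustment.** Control status is the same for everyone at baseline, so including it as an outcome time cannot account for how far above 140 mmHg a patient began. SBP itself could do so, but it is not among the named covariates.

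At stake is how the pilot's output is read. The Discussion makes a feasible and preliminarily effective intervention the route to a larger trial, and the slopes are meant to inform that trial's analysis strategy.

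**Working it through.** **The plan's own figure.** 4 physicians × 15 patients = 60, or 30 per arm. This reproduces. The article sets no power or effect size for the trial and gives no SBP mean or SD for its patients.

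**Step 1. Baseline control.** Entry: SBP ≥140. Control: SBP <140. The two exclude each other, so systolic control at baseline is 0 of 60. This takes the screening SBP as the baseline value; the article describes no other baseline reading. If Table 2 means 'or', a patient with SBP ≥140 and DBP <90 enters already controlled, and the 0 % no longer holds.

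**Step 2. Logistic model.** The log-odds for 0 of 30 is ln(0/30), which is minus infinity in each arm. The interaction against baseline, (month t − baseline) in one arm minus the same in the other, then subtracts one infinite term from another. The baseline level adds no information on the treatment contrast.

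**Step 3. Within-arm slope with no effect.** Let p be the chance of a reading below 140 at each follow-up visit.
- Times 0, 3, 6, 9; mean 4.5; deviations −4.5, −1.5, 1.5, 4.5.
- Sum of squares = 20.25 + 2.25 + 2.25 + 20.25 = 45.
- Expected values 0, p, p, p. Slope = p(−1.5 + 1.5 + 4.5)/45 = 0.1p per month, or 0.9p over nine months.
- From months 3, 6 and 9 only, the expected values are p, p, p and the slope is 0.

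The sign needs no assumption about variability. Only the size does.

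**Step 4. Size, on assumed inputs.** Simulation with no change in usual SBP. Assumed: source mean 145 or 155 mmHg, between-patient SD 15 or 20, visit-to-visit SD 8 to 15, selection on three readings ≥140, SBP criterion alone.

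| Quantity | Range |
|---|---|
| p, control at one given follow-up visit | 3.9 to 16.6 % |
| Patients of 30 (30p) | 1.2 to 5.0 |
| Slope, 0.1p per month | 0.4 to 1.7 points |
| Fitted rise over nine months, 0.9p | 3.5 to 14.9 points |
| p for entry SBP 140 to 149 | 14 to 25 % |
| p for entry SBP ≥170 | 0 to 8 % |

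With t-based intervals in arms of 30, the 95 % CI for the slope including baseline lies wholly above zero in 30 to 59 % of no-effect arms (mean 145, SD 15, visit SD 10 to 15), and in 3 to 23 % with mean 155, SD 20.

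**Step 5. Between arms.** With no effect both slopes have expectation 0.1p, so the difference is 0. The simulated difference in control at a visit was 0.000 at each visit SD tried (8, 12 and 15; mean 155, between-patient SD 15).

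**Step 6. A sustained-control rule.** Control on two visits occurs by noise in 1.0 to 5.0 % of patients, against 3.9 to 16.6 % for one visit. With a true 10 mmHg shift, the arm difference is 11 to 22 points for single-visit control and 6 to 14 points for control at both months 6 and 9. The stricter rule removes noise responders but also shrinks the contrast.

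**The case against.** The strongest reply is that the randomised comparison is untouched. The model takes group as its primary independent variable, noise falls equally on both arms in expectation, and nowhere does the article say that a within-arm slope will be read as efficacy. Entry at three encounters already reduces noise responders: entry on one reading would give 8.8 to 27.3 %. Change in clinic BP is also primary, so information above the limit is kept. All this stands and limits the point to the handling of baseline.

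It can also be said that a covariate list is usually left to the analysis plan. On its own, the absence of baseline SBP would not be worth raising. It matters here because the article does fix baseline as an outcome time, and for this binary outcome that cannot do the adjusting.

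Stronger readings are tempting, but the article does not support them:

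- *Control rests on one reading, so sustained control is not measured.* The objective speaks of an approach that "is feasible in improving sustained BP control among 60 recent Ghanaian stroke patients". Control is compared at months 3, 6 and 9, the last two after the intervention tactics cease, with per-patient trajectories. Persistence is measured; what is absent is a single summary that defines it.
- *A minimum fall in SBP should be required.* Control is a state, not a response. Adding an illustrative 10 mmHg fall still leaves 2.7 to 14.8 % of no-effect patients controlled.
- *Inflated success rates feed the next sample size.* The article names the ICC, variance estimates and covariance structure for that purpose, and says that pilots estimate effect size poorly.

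**Conclusion.** The point holds in a limited form. Baseline systolic control is fixed at 0 % by eligibility unless Table 2 means 'or', so using baseline as an outcome time in the control model is uninformative at best and unstable at worst. Within-arm control slopes that include it are positive in expectation for any non-zero p, by 0.1p per month. That result is algebra, for a p that is constant over the follow-up visits. The sizes (p of 3.9 to 16.6 %, and 14 to 25 % against 0 to 8 % by entry SBP) rest on assumed means and SDs and on the systolic criterion alone.

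A reader might infer that the trial's comparison is biased by noise. It is not, in expectation. With 30 patients and two physicians per arm, however, a chance imbalance in starting SBP is plausible, and no named covariate directly adjusts for it. This is a cheap improvement to the analysis text, not a flaw in the design.

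**What to change.** In Statistical analyses, Primary outcome measures:

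1. Fit the BP-control model to months 3, 6 and 9 only, with group, time and their interaction, and add continuous baseline SBP as a covariate.
2. Compute control slopes from the post-baseline visits, or label them and the within-arm percentages as descriptive.
3. State that preliminary effect is judged on the between-arm difference only.

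In Table 2, reconcile 'and or' so that one definition of control applies, and check whether any patient can then be controlled at entry.

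Optionally, report control at both months 6 and 9 as a supportive summary of sustained control. It should not replace control at each visit: it shrinks the contrast, leaves out month 3, and needs a rule for a patient who misses one of the two visits.

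The cost is wording. Baseline SBP and the month 3, 6 and 9 readings are already collected, and dropping baseline as an outcome time loses no information on systolic control.

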### Study participants

The participants will be 60 adult Ghanaian recent-stroke patients (within 1 month of stroke onset) with uncontrolled HTN who meet the inclusion/exclusion criteria. SBP ≥140 mmHg is used as the selection variable since most patients with HTN who are aged below 65 years have systolic or combination systolic/diastolic hypertension and, for the majority, controlling SBP results in diastolic blood pressure (DBP) also being controlled [43, 44].

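### Table 2 joins the two limits for blood pressure control with an undecided operator; read literally, it counts patients as controlled while their systolic pressure still meets the entry criterion

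*Protocol article*

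**What the plan says.** Under Outcome measures, the primary outcome is described thus: "This will include percent success in reaching BP control (Table 2) and changes in clinic BP measurements". Table 2 supplies the definition of control: "resting systolic blood pressure of <140 mmHg and or diastolic blood pressure of <90 mmHg". In Statistical analyses, the generalized linear mixed model takes "percent success reaching BP control (or resting BP changes individually) as the primary dependent variable (Table 2") and has baseline, 3, 6 and 9 months as its time points. The same section plans to estimate percent success for each subject at those four times.

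Eligibility uses systolic pressure only. Study participants states that "SBP ≥140 mmHg is used as the selection variable", on the ground that "for the majority, controlling SBP results in diastolic blood pressure (DBP) also being controlled". The inclusion criteria define uncontrolled hypertension by the same systolic limit. Recruitment applies it as "Subjects whose SBP averages ≥140 mmHg from the last two readings of the 10-min protocol". None of these sections sets a diastolic limit.

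Nothing else in the article settles the operator. The provider-level intervention mentions thresholds without values, and the abstract names blood pressure control as the primary outcome without defining it.

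**The concern.** A binary endpoint needs one rule that sorts every reading into success or failure. Table 2 gives two rules, and they disagree for every patient who has exactly one of the two pressures below its limit. Read literally, the wording is the inclusive *or*, so that reading is not strained.

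Under *or*, success no longer requires systolic pressure to fall, although systolic pressure is what made the patient eligible. Some patients would enter the longitudinal model as baseline successes in a trial that selected them for being uncontrolled. The operator could also be settled after the results are known. Finally, the article intends to use its variance and intracluster correlation estimates to size a later trial, so an unsettled endpoint would carry over into that design.

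**Working it through.** **1. Logic check (no assumptions).** Inputs are the two limits in Table 2 and the entry limit of SBP ≥140 mmHg.

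| Reading (mmHg) | Meets SBP entry limit | Controlled under *and* | Controlled under *or* |
|---|---|---|---|
| 150/85 | yes | no | **yes** |
| 150/95 | yes | no | no |
| 135/95 | no | no | **yes** |
| 135/85 | no | yes | yes |

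The first row is the conflict: one reading both qualifies the patient as uncontrolled and scores as a success. Under *and*, no reading with SBP ≥140 can be a success, so baseline control is 0% by construction when the baseline value is the qualifying reading.

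**2. Size at baseline (illustration).** The article gives no means, SDs or correlation. Assume bivariate normal SBP and DBP with SDs 18 and 12 mmHg and correlation 0.6, truncated at SBP ≥140. The share already controlled under *or* is

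P(DBP <90 | SBP ≥140) = [P(DBP <90) − P(SBP <140 and DBP <90)] / [1 − P(SBP <140)].

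| Assumed means before truncation | Calculation | Share |
|---|---|---|
| 150/85 | (0.662 − 0.262) / (1 − 0.289) | 56% |
| 155/90 | (0.500 − 0.170) / (1 − 0.202) | 41% |
| 160/95 | (0.338 − 0.099) / (1 − 0.133) | 28% |
| 165/100 | (0.202 − 0.052) / (1 − 0.082) | 16% |

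As a sensitivity check, a diastolic SD of 11 with correlation 0.5 to 0.7 and means from 150/90 to 160/95 gives about 25% to 40%.

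**3. Effect on the control rates.** P(*or*) = P(SBP <140) + P(DBP <90) − P(*and*), so P(*or*) can never be below P(*and*). With SDs 18/11, correlation 0.5 to 0.7 and follow-up means from 150/90 to 135/82, control is about 22% to 56% under *and* and 54% to 85% under *or*. At any given setting the gap is about 26 to 36 percentage points.

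**4. Effect on the between-arm difference.** The model is that of step 2 without truncation, with assumed follow-up means. Each cell gives the control-arm rate, the intervention-arm rate and the difference in points, which is taken from unrounded rates.

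| Control vs intervention means | Under *and* | Under *or* | Difference under *or* is |
|---|---|---|---|
| 150/90 vs 135/82 | 23.0%, 53.7%: 30.7 | 55.9%, 82.0%: 26.1 | smaller |
| 155/92 vs 140/85 | 15.9%, 42.3%: 26.5 | 47.7%, 73.8%: 26.1 | about equal |
| 160/95 vs 140/85 | 9.9%, 42.3%: 32.4 | 37.3%, 73.8%: 36.6 | larger |
| 160/95 vs 150/90 | 9.9%, 23.0%: 13.1 | 37.3%, 55.9%: 18.6 | larger |
| 165/100 vs 150/92 | 5.2%, 21.3%: 16.1 | 23.3%, 51.0%: 27.7 | larger |

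The direction depends on how high the pressures are.

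**The case against.** The strongest reply is that this is a drafting slip for *and*. The reason given for selecting on systolic pressure, that "controlling SBP results in diastolic blood pressure (DBP) also being controlled", treats systolic pressure as the one to bring down, and under *and* nothing in the article conflicts. That is a fair account of the likely intent, and it means the article does not contradict its entry rule outright: the conflict exists only under *or*. It does not remove the defect. The article states the definition itself rather than leaving it to another document, and the words as printed allow *or*. The quoted rationale also runs one way only; it does not say that a diastolic pressure below 90 implies systolic control.

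A second reply is that this is a 60-patient feasibility pilot, sized for precision, with no success threshold on the control rate. Change in clinic blood pressure is also a primary measure and does not depend on Table 2. Both facts stand and limit the consequences. Percent control is still listed first among the primary measures and is modelled as primary.

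A third reply is that the percentages are soft. They are: a spread of 16% to 56% shows that the article does not determine the size. Entry also requires SBP ≥140 at a pre-stroke encounter, a post-stroke encounter and screening. A single truncation does not model this, and the repeated rule would push the cohort toward higher pressures, where the illustrated share is smaller.

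A reader might also infer that *or* must dilute the treatment effect, since it inflates both arms. The working does not support that as a general statement: *or* narrows the difference in some settings and widens it in others.

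**Conclusion.** The point holds as an ambiguity in the definition of a primary endpoint. Its literal reading conflicts with the systolic entry rule. That finding follows from the definitions alone and needs no distributional assumption.

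Its size does need assumptions. Under those stated, roughly 16% to 56% of patients with SBP ≥140 would be baseline successes under *or*, against none under *and*, and follow-up control rates would differ by about 26 to 36 points between the readings. *Or* cannot lower the control rate in either arm; its effect on the between-arm difference has no fixed sign. The outcome of change in clinic blood pressure is unaffected. A wider conclusion, that the article contradicts its own eligibility definition under any reading, is not supported.

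**What to change.** Before analysis, replace the double conjunction in Table 2 with a single operator, reconciled with the entry rule so that no patient still at SBP ≥140 mmHg counts as a success. *And* (SBP <140 and DBP <90 mmHg) is the reading consistent with Study participants, Inclusion criteria and Recruitment. Apply it at baseline and at 3, 6 and 9 months in every analysis of percent success.

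No change to how follow-up readings are averaged is needed for this point. The last-two-readings rule belongs to screening, and no error is shown in follow-up measurement.

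The cost is a one-line amendment, and observed control rates will be lower than they would be under *or*.
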